### Secondary Endpoints

We expect that relative to placebo, lanicemine will demonstrate effects on neurophysiology measured on the fifth day of treatment, and on the CAPS-5 measured 3 days after the last infusion (day 8). The primary analyses for these endpoints are the regression of neurophysiology measures, measured after infusion 3, and CAPS-5, measured on day 8, onto treatment group after covariation for the respective baseline values. Secondary analyses will use multilevel models to evaluate changes as a function of stratification variables, treatment, time and the interaction of treatment and time. In addition, Bayesian Structural Equation Modeling will be used to test the hypothesis that treatment effects on day 5 APS or neurophysiology mediate treatment effects on day 8 CAPS-5.

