## Functional Mechanism

Behavioral sensitization refers to a process whereby trauma-associated stress (but also repeated use of substances of abuse, mood or anxiety episodes, and suicide attempts) sensitize behavioral, motivational and stress systems, thereby increasing the behavioral and physiological reactivity to subsequent stressors or other sensitizing agents even after a prolonged absence of those agents (15–18). Consistent with findings in animals, research in humans showed at least three different aspects of behavioral sensitization: *induction*, the development of behavioral sensitization to a sensitizing agent, including uncontrollable stressors (19), substances of abuse (18, 20, 21), and, in PTSD, repeated illness episodes (22); *expression*, exaggerated behavioral or physiological responses to a sensitizing agent even after prolonged absence of that agent (18, 21, 23); and c*ross-sensitization*, the process by which sensitization to one agent results in sensitization to other agents (e.g., facilitation of behavioral sensitization to psychostimulants after exposure to uncontrollable stress) (24). Animal research showed that all three aspects of behavioral sensitization require activation of NMDARs albeit *via* different neural pathways. Repeated cocaine administration increased NMDAR sensitivity only in rats that developed a sensitized motor response (25). Blockade of NMDARs by non-competitive NMDAR antagonist ketamine or MK-801 prevented *induction* of behavioral sensitization to ethanol (26, 27), apomorphine (28), stimulants (29–36), stress (36), and nicotine (37, 38), blocked *expression* of behavioral sensitization to alcohol (39), stimulants (29–32, 35, 40), stress (41), and nicotine (38), and blocked *cross-sensitization* between ethanol and stimulants (40, 42) and between stress and stimulants (36, 43, 44). Administration of MK-801 in the nucleus accumbens prevented induction but not expression of behavioral sensitization to stimulant administration (45), consistent with involvement of different neural pathways in induction and expression of behavioral sensitization.

Our premise for this study is that PTSD symptoms are associated with behavioral sensitization (46–48). We further propose that this type of sensitization could be blocked rapidly with an NMDAR antagonist (36, 43, 44) to relieve PTSD symptoms.

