## Study Design

This study is funded by the NIMH under an R61/R33 Phased Innovation Award (5R61MH110540). Biohaven Pharmaceutical Holding Company LTD provided material support. The study drug is administered as an intravenous solution under FDA IND number 134304; the trial is registered at ClinicalTrials.gov under NCT03166501. All study-related procedures and materials have been approved by the Baylor College of Medicine Institutional Review Board, and the MEDVAMC Office of Research and Development. An NIMH-appointed data and safety monitoring board (DSMB) provides oversight.

This study uses a randomized, double-blind, parallel-arm, placebo-controlled fixed dose design to test lanicemine (100 mg) compared to saline placebo in up to 24 male and female outpatients between the ages of 21 and 65 who have significant PTSD symptoms (CAPS-5 score of at least 25, and a Clinical Global Impression of Severity [CGI-S] score of at least 4), and physiological manifestations of behavioral sensitization (APS T-score of at least 2.8). Inclusion and exclusion criteria are displayed in **Supplemental Material**.

To qualify for randomization, entry criteria must be met at screening and the morning of the first lanicemine infusion. Subjects are randomized in a 1:1 ratio to receive three 60-min intravenous infusions of lanicemine or placebo on non-consecutive days over a 5-day period. **Table 1** provides the timeline of all study procedures. **Table 2** provides the timeline of study procedures at the first infusion (day 1) and third infusion (day 5).

**Table 1 T1:** Schedule of events.

	Screening^a^	Treatment period^b^			Telephone follow-up	EOS/ET^c^
	Day -42 to -1	Day 1 (1^st^ infusion)	Day 3 (2^nd^ infusion)	Day 5 (3^rd^ infusion)	Day 8 ± 2	Day 19 ± 4
Informed consent	X					
Eligibility criteria	X	X				
Demographics	X					
Psychiatric and family history	X					
Medication history	X	X	X	X	X	
Medical history	X					
Alcohol and drug history	X					
MINI	X					
CAPS-5	X	X			X	X
PCL-5	X	X			X	X
CGI-S^d^	X	X	X	X	X	X
CGI-I^d^	X	X	X	X	X	X
C-SSRS^d^	X	X	X	X	X	X
Vital signs (supine)^e^	X	X	X	X		X
Orthostatic BP^f^	X	X	X	X		
Physical examination	X	X				X
Weight, height, BMI	X	X				
Digital 12-lead ECG^g^	X	X	X	X		X
Metabolic panel	X	X				X
HgbA1c	X					
Serum pregnancy test	X					X
Urine pregnancy test^h^		X	X	X		
Urinalysis	X	X				X
Urine drug screen	X	X	X	X		X
Adverse events	X	X	X	X	X	X
PK sampling		X		X		
NPU-threat test		X		X		
Mismatch negativity (MMN)		X		X		

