### Specific Analytic Strategies

Efficacy and safety variables will be summarized using descriptive statistics and graphs. Continuous variables will be summarized by descriptive statistics. Categorical variables will be summarized in frequency tables. Pharmacokinetic variables will be summarized by the geometric mean and coefficient of variation. Lanicemine will be compared with placebo. Where appropriate, we will report model-based point estimates together with their 95% credible intervals.

Preliminary data analyses examining group differences for demographic and baseline variables will use cross-tabulation, ANOVA’s, and examination of correlations between baseline variables and specified outcomes. For the purposes of evaluating the comparability of groups, posterior probabilities of ≥95% will constitute evidence for statistically reliable differences. Baseline or demographic variables on which group differences are detected, and which are correlated with outcomes meet the definition of confounders (106, 107), and will result in two sets of analyses: one in which the relevant variable is included as a covariate and one in which it is not. This will permit determination of the degree to which any covariate might confound conclusions regarding treatment. The data analytic strategy will use generalized linear modeling (GLM) and multilevel models for both continuous and discrete outcomes. Cross-sectional continuous, count, dichotomous and time to event data will be evaluated using GLM and proportional hazards regression, respectively. All analyses will be conducted on a mITT analysis set.

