Assessing the convergence of Bayesian analyses on the posterior distributions *via* Monte-Carlo Markov chain (MCMC) will use graphical (Trace Plot, Autocorrelation Plot) and quantitative (Gelman-Rubin Diagnostics and Effective Sample Size) evidence. Mediational modeling will permit estimates of the indirect effects of treatment on primary and secondary endpoints using the product coefficient method (111). Bayesian Structural Equation Modelling (BSEM) prior specification will adapt recommendations from Muthén and Asparouhov (112). A Bayesian estimate for the indirect effect employs the posterior distribution of the parameter (i.e. the product coefficient): a density denoting the probability that the different values of the parameter obtain given the observed data. This posterior distribution may be further partitioned to evaluate the probability that the true parameter falls within a specific range of values. This will facilitate decision-making regarding the relative merits of continued investigation of the compound. Use of the MCMC approach in Bayesian analyses has demonstrated superiority for small sample performance compared to maximum likelihood-based approaches in continuous, normally distributed data (111). These properties are likely due to the MCMC approach’s lack of reliance on large sample size assumptions (113). Sensitivity analysis using optimistic and pessimistic, skeptical priors evaluates prior assumptions (110).

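### The mediation analysis reads the posterior of a product coefficient whose mediator-to-CAPS-5 path is not randomised, and nothing in the plan guards that path against shared causes of APS and CAPS-5

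*Protocol article*

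**What the plan says.** Under Secondary Endpoints, the article will use Bayesian structural equation modelling (BSEM) to "test the hypothesis that treatment effects on day 5 APS or neurophysiology mediate treatment effects on day 8 CAPS-5". Under Specific Analytic Strategies it names the estimator: "Mediational modeling will permit estimates of the indirect effects of treatment on primary and secondary endpoints using the product coefficient method". It also names the evidence: "A Bayesian estimate for the indirect effect employs the posterior distribution of the parameter (i.e. the product coefficient", and gives it a use: "This will facilitate decision-making regarding the relative merits of continued investigation of the compound".

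Three other statements bear on the point.

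- Study Design: "Subjects are randomized in a 1:1 ratio". Treatment is the only randomised quantity.
- Functional Mechanism: "Our premise for this study is that PTSD symptoms are associated with behavioral sensitization".
- Specific Analytic Strategies, on confounding: "Baseline or demographic variables on which group differences are detected, and which are correlated with outcomes meet the definition of confounders". This rule concerns imbalance between arms.

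The effect of treatment on CAPS-5 has its own regression, of "CAPS-5, measured on day 8, onto treatment group after covariation for the respective baseline values". The sensitivity analyses that the article names concern priors and missing data.

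**The concern.** Write the indirect effect as a × b, where a is the effect of treatment on the day 5 mediator and b is the slope of day 8 CAPS-5 on that mediator within arm. Randomisation protects a. It does not protect b: anything that makes a patient high on both APS and CAPS-5 enters b, whether or not changing APS would change CAPS-5.

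The article's own premise is that symptoms and sensitisation go together, so a non-zero b is to be expected from stable patient differences alone. If lanicemine then lowers APS, a × b is pushed below zero. When CAPS-5 has not moved, the model balances the books with a direct effect of opposite sign.

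The error therefore arises when the trial succeeds on its primary endpoint. That is when a claimed link from mechanism to symptoms would be most persuasive.

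**Working it through.** **Inputs.** From Sample Size: n = 20 (10 per arm), 24 recruited, and repeated-measures correlation 0.5. The article states no operating characteristic for mediation, so there is no figure of that kind to reproduce. Its 82% for the primary contrast does suggest a size for a. With flat priors:

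- SE = √(4/20) × √(1 − 0.5²) = 0.387.
- The rule P(d < −0.4) ≥ 0.75 is met when the estimate is below −0.4 − 0.674 × 0.387 = −0.661.
- At a true d of −1.0 the chance is Φ((1.0 − 0.661)/0.387) = 80.9%, and at −1.015 it is 81.9%.

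The article does not state the true effect behind its 82%, so a = −1.0 SD is an assumption consistent with that figure.

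**Null model (assumed).** APS and CAPS-5 are each a stable trait plus an independent state, with test-retest correlation 0.5. The traits correlate τ, so the cross-sectional correlation is k = 0.5τ. Neither lanicemine nor APS has any effect on CAPS-5. For τ = 0.3, 0.6 and 1.0, k = 0.15, 0.30 and 0.50.

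**Bias.** The true b is 0. The fitted b tends to:

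- no baselines: k
- own baseline only (CAPS-5 equation has baseline CAPS-5): 0.5k/(1 − k²)
- both baselines: [0.25k/(1 − k²)] / [(0.75 − k²)/(1 − k²)] = 0.25k/(0.75 − k²)

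Multiplying by a = −1.0 gives the false indirect effect, in SD of CAPS-5:

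| Baselines in model | τ = 0.3 | τ = 0.6 | τ = 1.0 |
|---|---|---|---|
| None | −0.15 | −0.30 | −0.50 |
| Own | −0.08 | −0.16 | −0.33 |
| Both | −0.05 | −0.11 | −0.25 |

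The total effect is zero, so the fitted direct effect is equal and opposite.

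**How often it would look like mediation.** Simulation with 10 per arm and flat-prior posteriors in place of the unspecified BSEM priors. Share of null trials with P(ab < 0) ≥ 0.95:

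| Baselines in model | τ = 0.3 | τ = 0.6 | τ = 1.0 |
|---|---|---|---|
| None | 9% | 17% | 46% |
| Own | 6% | 11% | 27% |
| Both | 4% | 7% | 17% |

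At τ = 0 the rate is about 3%. Repeat runs move these figures by up to about 3 percentage points. Rates for a 95% credible interval that excludes zero are about half as large: for τ = 0.6 to 1.0, 10% to 29% with no baselines, 6% to 15% with own and 3% to 9% with both.

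**Second parameterisation.** Put both baselines in the CAPS-5 equation and let an unmeasured common cause leave a residual correlation ρ. At n = 20 the 95% interval of ab excludes zero in 2%, 11%, 31% and 57% of trials for ρ = 0, 0.3, 0.5 and 0.7. In the trait model with both baselines, the implied ρ equals 0.25k/(0.75 − k²), that is 0.05, 0.11 and 0.25, so the two models agree.

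**Two limits.** More patients do not help: at n = 200 and ρ = 0.3 the interval excludes zero in 99% of trials. With no APS effect (a = 0), it does so in at most about 2% at ρ = 0.3 or 0.5.

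**The case against.** The strongest reply is that much of the criticised model is not in the article.

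- **Covariates.** The respective baselines are attached to the separate regressions, not to the BSEM. A journal article may leave the covariate set of a secondary model to the full plan. This stands: a reader might infer that baseline APS is excluded from the CAPS-5 equation, but the article does not say so. The point does not depend on it, since bias remains with both baselines.
- **Threshold.** No rule for declaring mediation is given. The analysis is framed as estimation, and the 0.95 cut-off is mine. This stands.
- **Size.** No figure in the article supports any particular τ, and τ = 1.0 is an extreme. At 0.3 with own baselines the 95% interval rate is about 4%. Enrolment requires an APS T-score of at least 2.8. Truncating APS at that cut-off lowers the interval rate with own baselines to about 4% at τ = 0.6 and 12% at τ = 1.0. With both baselines it is then about 4% and 9%. This stands too.
- **Consequence.** The Conclusion section starts the R33 study on change in APS and in neurophysiology, and the go rule is P(d < −0.4) ≥ 0.75. Mediation is in neither. The treatment effect on CAPS-5 is also reported in its own regression, so a null symptom result would be visible.
- **Generality.** An unrandomised mediator limits every product-coefficient analysis. True, but this article gives the result a role in decisions on the compound without stating the assumption.

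What the reply does not remove is that the article itself fixes the hypothesis, the estimator and the use, and that no stated safeguard reaches the b path.

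**Conclusion.** The point holds in a limited form and is worth acting on. The product-coefficient posterior can appear to support mediation when lanicemine has no effect on CAPS-5, provided that APS falls and that APS and CAPS-5 share causes. With an APS effect of −1.0 SD, the false indirect effect runs from −0.05 SD of CAPS-5 (both baselines, τ = 0.3) to −0.50 SD (no baselines, τ = 1.0). These figures rest on the assumed trait correlation, the assumed APS effect, flat priors and a borrowed threshold. With no shared trait there is no inflation.

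Three stronger readings are tempting and are not supported.

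- A reader might infer that mediation will be found whenever lanicemine lowers APS. The rates above are well short of that.
- A reader might infer that the R33 decision rests on mediation. The stated gate does not use it.
- A reader might infer that mediation must not be named unless the total CAPS-5 effect favours lanicemine. Such a gate would reduce false claims, but an indirect effect can exist alongside a small total effect, and the gate would cost power at n = 20 to 24. It is a choice, not a correction of an error.

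**What to change.** 1. In the BSEM, enter the day 1 values of both the mediator (APS or the neurophysiology measure) and CAPS-5 in both the mediator equation and the CAPS-5 equation.
2. Report the total and direct effects on CAPS-5 beside the indirect effect, so that an indirect effect offset by an opposite direct effect can be seen.
3. Repeat the indirect effect with the residual correlation between mediator and CAPS-5 fixed at a range of assumed values, for example 0 to 0.3. This spans the 0.05 to 0.25 that the trait model leaves after both baselines. The step is needed because the baselines reduce the bias without removing it.
4. Under Specific Analytic Strategies, describe the mediation result as exploratory and conditional on no mediator-outcome confounding, and qualify the sentence on its use in decisions accordingly.

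The baseline measures are already scheduled on day 1, so the cost is wording and a few more model runs. The downside is one or two degrees of freedom in a sample of 20 to 24 and a less favourable-looking mediation result.

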### Analysis Sets

Analyses will be performed on a:

Modified intent-to-treat (mITT) analysis set: this analysis set will include all randomized patients who took study medication, and who have a baseline APS and at least 1 post-baseline behavioral rating. The mITT analysis set will be used for exploratory efficacy analyses.

Per-protocol (PP) analysis set: This analysis set will include only those mITT patients without significant protocol deviation, and who received the treatment to which they were randomized. The analysis of the primary efficacy variable will be repeated on this set, and additional analyses of efficacy variables may be performed using this set to assess the robustness of the treatment effects.

Safety analysis set: This analysis set will include all randomized patients who were given at least one dose of study medication, on whom any post-dose data are available, and who are classified according to the treatment actually received (i.e., erroneously treated patients will be accounted for in their actual treatment group). This set will be used to assess safety and tolerability variables.

### Specific Analytic Strategies

Efficacy and safety variables will be summarized using descriptive statistics and graphs. Continuous variables will be summarized by descriptive statistics. Categorical variables will be summarized in frequency tables. Pharmacokinetic variables will be summarized by the geometric mean and coefficient of variation. Lanicemine will be compared with placebo. Where appropriate, we will report model-based point estimates together with their 95% credible intervals.

Preliminary data analyses examining group differences for demographic and baseline variables will use cross-tabulation, ANOVA’s, and examination of correlations between baseline variables and specified outcomes. For the purposes of evaluating the comparability of groups, posterior probabilities of ≥95% will constitute evidence for statistically reliable differences. Baseline or demographic variables on which group differences are detected, and which are correlated with outcomes meet the definition of confounders (106, 107), and will result in two sets of analyses: one in which the relevant variable is included as a covariate and one in which it is not. This will permit determination of the degree to which any covariate might confound conclusions regarding treatment. The data analytic strategy will use generalized linear modeling (GLM) and multilevel models for both continuous and discrete outcomes. Cross-sectional continuous, count, dichotomous and time to event data will be evaluated using GLM and proportional hazards regression, respectively. All analyses will be conducted on a mITT analysis set.

Bayesian approaches will implement joint modeling of observed outcomes and the missing data which is robust to ignorable missingness (108). Sensitivity analyses will evaluate robustness of analytic conclusions to missing data. Non-ignorable missing data patterns will be addressed through pattern-mixture modeling methods (109). Evaluation of posterior distributions will permit statements regarding the probability that effects of varying magnitudes exist, given the data. Specification of diffuse, neutral priors will reflect the initial uncertainty regarding effect sizes. For all generalized linear mixed models, priors for regression coefficients will be specified as ∼Normal (µ = 0, σ^2^ = 1 x 10^6^); level one error variances will be specified as ∼Folded t-distribution (ν = 3, µ = 0, σ = 1000). Prior distributions for level-two variances in multilevel models will follow ∼Folded t-distribution (ν = 3, µ = 0, σ = 1000). Priors for the comparison of proportions will be specified as ∼Beta (α = 0.5, β = 0.5). Sensitivity analysis using optimistic and pessimistic, skeptical priors will evaluate prior assumptions (110). Decisions regarding the degree to which treatment confers benefit, and whether further confirmatory trials are warranted will be based on the posterior distribution of effect sizes. If the observed posterior probability of a Cohen’s d < -0.4 is at least 0.75, this will be sufficient evidence to proceed to a larger POC clinical trial.

Assessing the convergence of Bayesian analyses on the posterior distributions *via* Monte-Carlo Markov chain (MCMC) will use graphical (Trace Plot, Autocorrelation Plot) and quantitative (Gelman-Rubin Diagnostics and Effective Sample Size) evidence. Mediational modeling will permit estimates of the indirect effects of treatment on primary and secondary endpoints using the product coefficient method (111). Bayesian Structural Equation Modelling (BSEM) prior specification will adapt recommendations from Muthén and Asparouhov (112). A Bayesian estimate for the indirect effect employs the posterior distribution of the parameter (i.e. the product coefficient): a density denoting the probability that the different values of the parameter obtain given the observed data. This posterior distribution may be further partitioned to evaluate the probability that the true parameter falls within a specific range of values. This will facilitate decision-making regarding the relative merits of continued investigation of the compound. Use of the MCMC approach in Bayesian analyses has demonstrated superiority for small sample performance compared to maximum likelihood-based approaches in continuous, normally distributed data (111). These properties are likely due to the MCMC approach’s lack of reliance on large sample size assumptions (113). Sensitivity analysis using optimistic and pessimistic, skeptical priors evaluates prior assumptions (110).

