## Secondary Outcome Measures

### Biomarkers of NMDAR Target Engagement

NMDAR target engagement is examined with neurophysiological measures that are translatable between animal and human studies.

Subanesthetic doses of NMDAR antagonist ketamine increased resting-state gamma band (30–100 Hz) power in animals (74–76) and humans as a function of time since start of ketamine infusion, rapidly normalizing after end of infusion (69, 77, 78). This response has been associated with activation of α-amino-3-hydroxy-5-methyl-4-isoxazolepropionic acid receptors (AMPAR) (79) or activation of fast-spiking gamma-aminobutyric acid (GABA)-ergic parvalbumin interneurons (80) following a ketamine-driven increase in prefrontal glutamate (81). Lanicemine 75 mg and 150 mg increased midline electrodes gamma band activity in a dose-response fashion in healthy volunteers (69). This increase was unrelated to increased motor activity, separating it from ketamine-increased gamma band power that did correlate with enhanced motor activity (69). Ketamine-increased gamma band power was unrelated to treatment response in patients with TRD (78). We hypothesize that resting state gamma band power will increase with lanicemine 100 mg compared to placebo.

The 40 Hz auditory steady state response (40 Hz ASSR) measures stimulus-evoked gamma band (40 Hz) power and phase synchronization. In awake rats, a single intravenous bolus of 1, 3, 10, and 30 mg/kg ketamine increased intracranial frontocentral 40 Hz power, but the time was delayed or duration prolonged linearly with increase in dose (82). Phase synchrony decreased at the lowest dose and increased at the highest dose, with changes correlating negatively with ketamine NMDAR occupancy (82). A single dose of MK-801 increased intracranial 40 Hz phase synchrony but did not affect power (83). In healthy humans and humans with schizophrenia, memantine 20 mg increased frontal 40 Hz power and phase locking; memantine 10 mg had no effects (84). We expect lanicemine 100 mg to increase 40 Hz ASSR power and phase synchrony.

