The auditory Mismatch Negativity (MMN) is evoked between 100 and 250 ms after an unexpected auditory event, and is measured as the difference between (frequent) expected and (infrequent) unexpected stimuli in a passive oddball task (85). MMN amplitude could be increased in PTSD (64, 86, 87), although this has not been found uniformly (88). MMN in healthy volunteers was increased under threat of an aversive stimulus (89) suggesting it could be sensitive to behavioral sensitization. Ketamine suppressed MMN amplitude (90–92), perhaps *via* blockage of NR2B receptor units (93), without affecting temporally overlapping ERP components (92). This effect is sustained for at least 30 min after end of infusion (92). Memantine could increase MMN amplitude (94). MMN amplitude is included as a measure of target engagement as well as a measure associated with functional mechanism. We expect suppression of MMN amplitude with lanicemine compared to placebo, potentially associated with change in APS.

P50 auditory sensory gating measures P50 amplitude suppression following presentation of the same auditory stimulus in short temporal proximity, reflecting pre-attentional information filtering (95–98). P50 gating is impaired in PTSD compared to trauma controls (99), and after acute stress in healthy individuals (100, 101). Lanicemine may normalize P50 gating if lanicemine attenuates stress reactivity. However, ketamine 0.3 mg/kg (bolus) in healthy volunteers impaired P50 gating through ketamine-induced increases in gamma band activity for the second stimulus of the repetition (102) which was also found in rats (76). Thus, lanicemine may normalize or worsen P50 gating. We study effects of lanicemine on P50 gating to examine this apparent discrepancy and in order to characterize its effects on aspects of information filtering.

Further specifics of the paradigms can be found in **Supplemental Materials**.

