This study is funded under an R61/R33 Phased Innovation Award (R61 MH10540-01). This award consists of an R61 POM study followed by an R33 phase to test clinical efficacy of a study drug. The R33 study would only commence if the POM study shows evidence of engagement by lanicemine of the functional mechanism (change in APS) and the biological target (change in neurophysiological measures). The go/no-go framework for the R61 study is operationalized such that if there is significant symptom improvement without a clear effect of functional mechanism and evidence of target engagement, the drug would not be tested further in an R33. A potential risk of this approach is that the measures of functional mechanism and of target engagement selected may not be appropriate even if the drug does engage the proposed mechanisms. This approach is in marked contrast to usual industry-supported early phase trials in which early signals of clinical efficacy drive the decision to move forward with larger Phase 2 studies, irrespective of information gleaned from biomarkers.

In conclusion, this study tracks engagement of the study drug on a functional mechanism likely to cut across disorders, which is consistent with recent NIMH-industry collaborative studies (114) and “Fast-Fail” trials (2, 115), and could serve as a template for testing pharmacological agents in psychiatry.

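### Two incompatible go rules: the APS threshold alone is called sufficient, but the Conclusion requires neurophysiological engagement as well

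*Protocol article*

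**What the plan says.** The first rule closes the discussion of priors in the Protocol article, Specific Analytic Strategies. The condition is "If the observed posterior probability of a Cohen’s d < -0.4 is at least 0.75" and the consequence is "this will be sufficient evidence to proceed to a larger POC clinical trial". The sentence names no endpoint and adds no second condition. The Sample Size section attaches the same threshold to the APS contrast and gives an 82% chance of detecting superiority with 20 subjects and r = 0.5, from 500 simulations.

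The second rule is in the Conclusion. The present R61 trial is "followed by an R33 phase to test clinical efficacy of a study drug", and the link between the two is explicit: "The R33 study would only commence if the POM study shows evidence of engagement by lanicemine of the functional mechanism (change in APS"). That sentence goes on to require the same for the drug's target, as shown by the neurophysiology. The same paragraph adds that symptom improvement without evidence on mechanism and target would end testing.

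For the neurophysiology, Biomarkers of NMDAR Target Engagement gives directions for most measures. For resting EEG: "We hypothesize that resting state gamma band power will increase with lanicemine 100 mg compared to placebo". The 40 Hz steady-state response is expected to rise and mismatch negativity amplitude to be suppressed. P50 is left open: "Thus, lanicemine may normalize or worsen P50 gating". Secondary Endpoints places the main neurophysiology analysis after infusion 3, adjusted for baseline.

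**The concern.** The go/no-go decision is what this trial is for. The Introduction says the funder's approach demands a biomarker of target engagement as well as one of the functional mechanism, and the Conclusion follows that. The sentence in Specific Analytic Strategies drops the target half.

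The case on which the two rules part is not exotic. It is a drug that lowers APS without a demonstrable effect on the NMDAR measures, which is what the target-engagement requirement exists to catch. With both rules in print, the choice between them could be made after the results are known. A reader could also take the 82% as the chance of a go, although it covers one of two required components.

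**Working it through.** **Logic.** Let A be the event that APS meets the threshold, and B the event that neurophysiology shows engagement.

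- Specific Analytic Strategies: A implies go.
- Conclusion: go implies A and B.
- Together these would make A imply B, which the data need not satisfy. Whenever A occurs without B, the rules give opposite answers.

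One inference is needed: that the larger proof-of-concept trial in the first rule is the R33 study. The article does not equate them word for word, but it describes no other successor.

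**The plan's own figure.** Inputs from Sample Size and Study Design: 20 subjects allocated 1:1, so n = 10 per arm; r = 0.5; threshold d < -0.4 with probability 0.75. With a flat prior and baseline-adjusted regression:

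- SE = sqrt(1 - r²) × sqrt(2/n) = sqrt(0.75) × sqrt(0.2) = 0.387
- A occurs if the estimate is at or below -0.4 - 0.6745 × 0.387 = -0.661
- P(A) = Φ((-0.661 - d)/0.387)

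This gives 0.044 at true d = 0, 0.25 at -0.4, 0.64 at -0.8 and 0.81 at -1.0. Simulating the regression with posterior draws gave 0.045, 0.247, 0.629 and 0.781, so the approximation runs slightly high at the larger effects. The article does not state the true effect behind its 82%, so that figure cannot be strictly reproduced. It is reached at a true d of about -1.02 here, about -1.11 with change scores, and -0.84 to -0.90 if 20 is read as per arm. The contradiction does not depend on which applies.

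**How often the rules would disagree (illustrative).** Assumptions not in the article: the APS effect is set so that P(A) = 0.82; B is one neurophysiology measure with the mirrored criterion, posterior probability at least 0.75 that d > +0.4; it has the same n and r, and is independent of APS. Then P(disagree) = 0.82 × (1 - P(B)) and P(go under both) = 0.82 × P(B).

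| True neurophysiology effect (SD) | P(B) | Go under both rules | Rules disagree |
|---|---|---|---|
| 0 | 0.044 | 0.036 | 0.784 |
| 0.4 | 0.25 | 0.205 | 0.615 |
| 0.8 | 0.64 | 0.525 | 0.295 |
| 1.02 | 0.82 | 0.672 | 0.148 |

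Positive dependence between APS and the measure would lower the last column. It cannot fall below 0.82 - P(B), which is 0.776, 0.57, 0.18 and 0 in the four rows. For an unaffected target, therefore, the disagreement barely depends on the independence assumption.

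**The case against.** The strongest reply is that the intended rule can be recovered. The Conclusion sets out the dual requirement at length, so the sentence in Specific Analytic Strategies may be loose shorthand for the APS part. The identity of the two follow-on trials is also inferred. Both points have weight, and they make this a matter of wording rather than of design. They do not remove the conflict: the shorter sentence is the only numerical decision rule in the analysis plan, and it says sufficient.

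A second reply is that a numerical criterion for target engagement may sit in the full protocol or analysis plan, which is not shown. That is fair, and its absence from the article is not held against it here. A cut-off elsewhere would still not reconcile the two published statements.

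Three stronger readings are tempting, and the article does not support them.

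- *The threshold has the wrong sign for gamma power and the 40 Hz response, which are expected to rise.* Sample Size ties d < -0.4 to APS, where a fall is expected, and nothing in the article applies it to the EEG measures. The sign would mislead only if the sentence, which names no endpoint, were taken to cover every endpoint.
- *The target condition is easily met by chance because any one of many measures and times would do.* The Conclusion speaks of measures in the plural and does not say that any one suffices. Secondary Endpoints also restricts the main analysis to after infusion 3. And since APS must pass too, a drug inactive on APS could reach a joint go at most 4.4% of the time under the calculation above, however loose the EEG condition.
- *The 82% is wrong.* It is stated for the APS contrast, and is attainable under an effect that the article does not give.

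**Conclusion.** The contradiction stands. One section makes the APS threshold enough to proceed; another makes neurophysiological engagement an additional requirement. A trial that meets the first without the second has no single answer.

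The conclusion rests on reading the next proof-of-concept trial as the R33 study, and on taking the unnamed endpoint to be APS, as Sample Size does. The probabilities of disagreement, about 0.78 with an unaffected target falling to about 0.15 at a true effect of about 1 SD, show that the conflict could well arise. They depend on the mirrored criterion, the single measure, independence and the chosen APS effect, and are not properties of the plan. The same holds for the 0.67 joint chance when each component passes 82% of the time (0.82 × 0.82 = 0.67).

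**What to change.** Before unblinding, amend the sentence in Specific Analytic Strategies in three respects:

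1. Name APS as the endpoint, and say that a posterior probability of at least 0.75 for d < -0.4 on APS is necessary but not sufficient.
2. Say that a go also requires the target-engagement condition of the Conclusion, judged in the direction hypothesised under Biomarkers of NMDAR Target Engagement, on a measure and time point that the sponsor prespecifies. The time should agree with Secondary Endpoints (after infusion 3); a time during the infusion would require that section to change too. Which measure to choose is the sponsor's decision. P50 should not satisfy the condition by itself, because its direction is not fixed.
3. Say explicitly that the larger proof-of-concept trial is the R33 study, if that is meant.

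In Sample Size, state that the 82% is the chance of meeting the APS component only, not the chance of a go.

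The change is to wording and needs no new subjects or procedures; the article reports 23 of 24 subjects already randomized. The cost is that a neurophysiology criterion must be committed to in advance, and that the chance of a go under the joint rule will be below 82%.
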